## Abstract

**Introduction:**

Studies show, malnourished women of childbearing age with environmental enteric dysfunction (EED) exhibit small intestinal enteropathy resembling that in malnourished children residing in the same community. However, currently there are no universally accepted protocols for validation of these facts. Our current protocol is designed to better understand the mechanism of transmission of the microbiota of mothers with EED to their children perpetuates intergenerational undernutrition. We plan to compare the small intestinal (SI) and fecal microbiota along with plasma, duodenal, and fecal proteomes/ metabolomes and histopathologic evidence of EED in non-pregnant women with and without malnutrition. We also plan to see and compare the effect of microbiota-directed balanced energy protein (MD-BEP) supplementation on these biological parameters between malnourished non-pregnant and pregnant women.

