### Methods and analysis

This is a community-based intervention study where participants will be enrolled in two cohorts: undernourished pregnant (BMI < 18.5 kg/m^2^; 18–35 years, *n* = 60) and undernourished non-pregnant ((BMI < 18.5 kg/m^2^; 18–35 years, *n* = 60) women from Bauniabadh and adjacent slum areas of Mirpur, Dhaka. For comparison, well-nourished pregnant women (BMI 20–24.9 kg/m^2^; 18–35 years, *n* = 30), who will be screened through household surveys from the Bauniabadh and adjacent slum area of Mirpur, Dhaka, and well-nourished non-pregnant (BMI 20–24.9 kg/m^2^; 18–35 years, *n* = 30) women of reproductive age will be recruited. We will use two specific aims, AIM 1 A and AIM 1B. In AIM 1 A, we will compare the small intestinal (SI) and fecal microbiota and the plasma, duodenal, and fecal proteomes/metabolomes of the undernourished non-pregnant cohort with histopathologic evidence of EED with the well-nourished non-pregnant cohort with no histopathologic evidence of EED undergoing routine endoscopic evaluation for dyspepsia. Upper gastro-intestinal (UGI) endoscopy will be performed on non-pregnant women and biopsy samples will be collected for diagnosis of EED and histopathological scoring. In AIM 1B, we will perform an intervention study. After UGI endoscopy, undernourished non-pregnant cohort will be randomized into two groups (*n* = 30/arm) and receive daily dietary supplementation with either shelf-stable microbiota-directed balanced energy protein (MD-BEP) or ready-to -use supplementary food balanced energy protein (RUSF-BEP) for 90 days. After cessation of the intervention they will be further followed up for another 270 days and biological samples will be collected at scheduled time points. The well-nourished non-pregnant cohort will not receive any nutritional intervention will serve as a reference control group. The undernourished pregnant cohort will also be randomly (*n* = 30/arm) assigned to receive either MD-BEP or RUSF-BEP daily for 6 months until the child birth and thereafter for 3 months and followed up for another 9 months. During this period anthropometry will be measured and biological samples including fecal and plasma samples will be collected from the mothers and their infants in scheduled time points. The well-nourished pregnant cohort will not be supplemented with MD-BEF or RUSF-BEP but will be followed-up with anthropometric measurement and sample collection like undernourished pregnant cohort. Due to ethical concerns related to performing endoscopy in pregnant women, UGI endoscopy in pregnant women will not be performed. Anthropometric, socio-demographic, and laboratory assay data will be compared across study groups. Additionally, potential EED biomarkers will be evaluated for correlations with nutritional status and histopathological findings, alongside analyses of the microbial community structure. Prior to participation, each subject will receive a comprehensive explanation of the study and provide written informed consent. Participants capable of signing will do so, while those unable to sign will provide a thumb impression as an alternative. A separate consent form specific to endoscopy and supplemental interventions will be administered, following the same consent procedure. The endoscopy consent form thoroughly details all aspects of the procedure, including associated risks, ensuring complete transparency. No information pertinent to the participant’s understanding is withheld. While enrolling the neonates, a signed written informed consent from the parents or guardians is obtained. All consents are obtained and documented in presence of the study physician at the study field office in front of a witness, who also sign the document as the witness. This study was conducted and reported in accordance with the CONSORT guidelines. The first participant was enrolled on 28 April 2023. Estimated end date is 31 December 2026. The schedule of study events is presented in Fig. 1.

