### AIM 1A: non-pregnant cohort

In AIM 1 A, for the healthy group, we plan to recruit a cohort of well-nourished Bangladeshi women who will undergo esophagogastroduodenoscopy (EGD) for evaluation of functional dyspepsia and identify 30 well-nourished participants who have normal duodenal mucosal histology. Healthy women (BMI 20–24.9 kg/m^2^) of childbearing age who have been referred for evaluation of functional dyspepsia as defined by Rome IV criteria, will be enrolled from women attending the Gastroenterology OPD of Bangladesh Specialized Hospital (BSH), Dhaka, Bangladesh, and also from the community who meet the inclusion criteria. Duodenal biopsies, duodenal aspirates, plasma and fecal specimens from these participants at the time of endoscopy and serial plasma and fecal samples will be collected according to the follow-up schedule (Fig. 3). These women will be considered as the control group for the non-pregnant cohort and will be followed for 360 days but will not receive any nutritional intervention. Undernourished (< 18.5 kg/m^2^; 18–35 years) women of childbearing age will be enrolled from Bauniabadh and adjacent slum areas of Mirpur, Dhaka, and EGD will be performed among 60 women at icddr, b Dhaka Hospital, or BSH, Dhaka. Participants will be screened through household surveys from the Bauniabadh and adjacent slum area of Mirpur, Dhaka. After EGD, the undernourished women will be randomized into two groups (*n* = 30/arm) and receive daily dietary supplementation with either MD-BEP or RUSF-BEP for a period of 90 days, with a further 270 days of follow-up after cessation of the intervention, and biological samples will be collected from the participants according to the schedule. The EGD scheme is presented in Fig. 2.

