### Sample size calculation and outcome

For normal-BMI (BMI 20–24.9 kg/m^2^) women of childbearing age or healthy volunteers undergoing EGD, the goal is to identify 30 normal-BMI participants who will undergo EGD for evaluation of functional dyspepsia and will have normal duodenal mucosal histology. We plan to recruit 100 individuals for EGD, and anticipate that 60 will have duodenal mucosa without macroscopic evidence of active acid-peptic disease, of whom 30 will have normal duodenal mucosal histology. These calculations are based on the team’s gastroenterologist who has 15-year experience with > 30,000 subjects from this socioeconomic group and geographic locale. These specimens from normal BMI participants without enteropathy will be compared with those of 60 undernourished low-BMI (< 18.5 kg/m2) women of childbearing age. As this is an experimental study, no formal power calculation has been performed for this exploratory research study. The same applies for the pregnant cohort.

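### Histopathologic EED is listed as a compared outcome, but the well-nourished group is selected on normal histology, so that comparison is circular and should be dropped or rebuilt on unselected women

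*Protocol article*

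**What the plan says.** Three parts of the protocol article bear on this.

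- **Abstract, Introduction.** The list of things to be compared includes "histopathologic evidence of EED in non-pregnant women with and without malnutrition", next to the microbiota, proteomes and metabolomes.
- **AIM 1A: non-pregnant cohort, and Sample size calculation and outcome.** The well-nourished group is found by endoscopy. The aim is to "identify 30 well-nourished participants who have normal duodenal mucosal histology". The sample size section gives the expected yield. Out of 100 women endoscoped, the investigators "anticipate that 60 will have duodenal mucosa without macroscopic evidence of active acid-peptic disease, of whom 30 will have normal duodenal mucosal histology". As to the use made of the material, the same section says: "These specimens from normal BMI participants without enteropathy will be compared with those of 60 undernourished low-BMI" women.
- **Methods and analysis (in the Abstract and in the main text).** Aim 1A sets undernourished women who have histopathologic EED against a "well-nourished non-pregnant cohort with no histopathologic evidence of EED undergoing routine endoscopic evaluation for dyspepsia". What is compared there is microbiota, proteomes and metabolomes. Histology defines the groups.

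The section Histopathology definition of EED grades EED from 0 (none) to 3 (severe).

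**The concern.** The characteristic that the Abstract proposes to compare is the entry criterion for one of the two groups. The well-nourished women cannot show EED, because any who did would not have been kept. The difference in EED between the groups therefore reflects how the controls were chosen as well as any effect of nutritional status, and the two cannot be separated.

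The yield figures show that the selection is not trivial: half of the well-nourished women who pass the macroscopic screen are expected to be set aside for abnormal histology. If the Aim 1A restriction to undernourished women with EED is applied as well, the contrast becomes 100% against 0% by definition.

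What is at stake is a finding that EED is more frequent or more severe in malnourished women. It would be easy to report from these data, and this sample cannot support it.

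**Working it through.** **Inputs from the protocol article**
- Undernourished non-pregnant women endoscoped: 60.
- Well-nourished women kept: 30, all with normal histology. Taking normal histology as Grade 0, EED is 0/30.
- Significance level: 0.05 (Data analysis). Sidedness is not stated; two-sided is assumed.

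**The plan's own figures.** No power calculation is given, so there is none to reproduce. The recruitment yield is consistent: 100 × 0.60 = 60 without macroscopic disease, and 60 × 0.50 = 30 with normal histology. It follows that 60 − 30 = 30 women, or 50% of those 60, are expected to have abnormal histology and are not kept.

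**Step 1: the count that gives significance against 0/30.** The article names no test for this comparison. Fisher's exact test is used here for illustration.
- 7/60 against 0/30: p = 0.09.
- 8/60 against 0/30: p = 0.048.

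So 8 of 60 undernourished women with EED (13.3%) is enough.

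**Step 2: how often that happens when nutrition makes no difference.** Let the true EED rate be π in both nutritional groups. Selection holds the control count at 0, so the chance of a significant excess in malnutrition is P(X ≥ 8) with X ~ Binomial(60, π).

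| True EED rate in both groups (assumed) | Probability of a significant excess in malnutrition |
|---|---|
| 5% | 0.01 |
| 10% | 0.25 |
| 15% | 0.70 |
| 20% | 0.93 |
| 30% | 0.999 |
| 50% | about 1 |

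At 50% the expected table is 30/60 against 0/30, with p = 2 × 10⁻⁷.

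**Step 3: the same question without selection on histology.** Take all 60 well-nourished women who pass the macroscopic screen, against 60 undernourished women. With a true rate of 50% in both groups, the two-sided Fisher test rejects with probability 0.035 in total, both directions together. Power is 0.998 for 90% against 50%, and 0.76 for 75% against 50%. The 90% is the enteropathy rate that the article's Introduction reports for malnourished women in an earlier study; 75% is an assumption. These figures treat the two groups as otherwise comparable, which the design does not secure.

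**The case against.** The strongest reply is that the comparison appears in one clause of the Abstract and nowhere in the operational text. Methods and analysis uses histology to define the Aim 1A groups, and the sample size section speaks of comparing specimens. The tests named in Data analysis concern baseline characteristics of the two intervention arms, and the models that follow address intervention effects and changes in weight and BMI. No test of EED by nutritional status is named. The stated hypothesis concerns the contribution of the small intestinal microbiota to enteropathy and malnutrition, not the prevalence of EED by BMI group. The study is also declared exploratory.

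Most of this stands. Choosing histologically normal controls is a legitimate way to obtain a reference for the microbiota and omics contrasts, and the Fisher test above illustrates a consequence; it is not a planned analysis. It does not remove the point, because the Abstract still announces a comparison that the stated selection makes uninterpretable. Exploratory status does not make a result fixed by selection informative.

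Three stronger readings are tempting and go too far.
- A reader might infer that the comparison shows a significant excess whatever the truth. It does not: at a true rate of 10% the probability is 0.25, and at 5% it is 0.01.
- A reader might take 50% as the EED rate in well-nourished women. It covers abnormal histology of any kind, in women evaluated for dyspepsia, and rests on clinical experience, so for EED in those women it is an upper figure.
- A reader might conclude that Aim 1A as a whole is invalid. The omics contrasts and the randomised comparisons do not depend on the clause at issue.

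**Conclusion.** The point holds as an inconsistency with a real consequence for interpretation. The Abstract lists histopathologic EED as a compared parameter, while the selection rules fix it at 0/30 in the well-nourished group. Any test of EED frequency or grade between the selected groups is circular. With equal true rates it would indicate an excess in malnutrition with probability 0.25 at 10%, 0.93 at 20% and about 1 at 50%.

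This rests on four assumptions: normal histology means Grade 0; all 60 undernourished women enter the comparison; the test is a two-sided Fisher test at 0.05; and the common EED rates are illustrative. The circularity itself depends only on the first.

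**What to change.** **Wording change.** State that histology is a group-defining criterion for Aim 1A and will not be tested between the selected groups. Remove histopathologic EED from the compared parameters in the Abstract. Keep the 30 women with normal histology as the reference for the microbiota, proteome and metabolome contrasts.

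**If EED by nutritional status is to be reported.** Retain the 0–3 grades of all well-nourished women biopsied without macroscopic acid-peptic disease (about 60) and compare them with all 60 undernourished women endoscoped. Describe the result as exploratory. This removes the selection on outcome but not the other differences between the groups: the well-nourished women are dyspepsia patients, partly from a hospital outpatient department, screened on mucosal appearance, whereas the undernourished women come from household surveys with no such screen stated.

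**Cost.** Small. The biopsies of the roughly 60 women have to be read in any case to find the 30 with normal histology, so no further procedure is needed. The grades of the roughly 30 women not kept must be retained, and consent must cover that use. The histology contrast will probably be smaller than the one that selection would produce.

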**Methods and analysis:**

This is a community-based intervention study where pregnant women and non-pregnant women of reproductive age (18-35 years) will be screened through household surveys from the Bauniabadh and adjacent slum area of Mirpur, Dhaka (pregnant and non-pregnant cohorts, n=90 each). Using Body Mass Index (BMI), both the groups will be categorized into undernourished (BMI <18.5kg/m2, n=60 each with pregnant and non-pregnant cohort) and well-nourished (BMI >20-24.9 kg/ m2, n=30, each with pregnant and non-pregnant cohort). Upper gastro-intestinal (UGI) endoscopy will be performed on non-pregnant women (both well-nourished and undernourished cohorts) and biopsy samples will be collected for diagnosis of environmental enteric dysfunction (EED) by histopathological scoring. We will compare the small intestinal (SI) and fecal microbiota and the plasma, duodenal, and fecal proteomes/ metabolomes of the undernourished non-pregnant cohort with histopathologic evidence of EED with the well-nourished non-pregnant cohort with no histopathologic evidence of EED (Aim IA). Furthermore, we will perform an intervention study (Aim IB). The undernourished non-pregnant cohort will be randomized into two groups (n=30/arm) and receive daily dietary supplementation with either shelf-stable microbiota-directed balanced energy protein (MD-BEP) or ready-to -use supplementary food balanced energy protein (RUSF-BEP) for 90 days. After cessation of the intervention they will be further followed up for another 270 days and biological samples will be collected at scheduled time points. The well-nourished non-pregnant cohort will not receive any nutritional intervention will serve as a reference control group. The undernourished pregnant cohort will also be randomly (n=30/arm) assigned to receive either MD-BEP or RUSF-BEP daily for 6 months until the child birth and thereafter for 3 months and followed up for another 9 months. During this period anthropometry will be measured and biological samples including fecal and plasma samples will be collected from the mothers and their infants in scheduled time points. Anthropometric, socio-demographic and laboratory assay data will be compared between the groups and candidate EED biomarkers will be correlated with nutritional status, histological analyses and score of EED, plus assessments of microbial community structure will be examined.

**Ethics and dissemination:**

Ethics approval was obtained from the Ethical Review Committee of icddr,b (protocol no: PR-22117; Version 1.2; 29 November 2022). The running approved protocol version is v1.3, dated 07 May 2024. Results of this study will be submitted for publication in peer-reviewed journals.

**Trial registration number:**

ClinicalTrials.gov ID: NCT05862363. Registered on 08 February 2023. https://clinicaltrials.gov/study/NCT05862363.

## Introduction

South Asia bears the highest global burden of undernutrition among women of reproductive age, with prevalence estimates ranging from 10% to 40%. In Bangladesh, the situation is especially concerning, as over 30% of women in this age group are undernourished—among the highest rates observed in developing countries. Maternal undernutrition is a significant determinant of poor birth outcomes, contributing to increased risks of low birth weight, neonatal mortality, and ongoing malnutrition in early childhood. It is estimated to be responsible for approximately 25% to 50% of intrauterine growth restriction. In such a way, nutritional deficits can be passed from mothers to their children, resulting in an intergenerational cycle of undernutrition [1]. In Bangladesh, half of the children under five living in slums experience stunted growth, compared to one-third in non-slum areas [2].

Addressing intergenerational malnutrition—whether through prevention or treatment—remains an urgent and unmet global health priority. Data are scarce on the contribution of the small intestinal (SI) microbiota to pathogenesis, primarily due to the difficulty in obtaining gut biopsy specimens from malnourished individuals. The Bangladesh Environmental Enteric Dysfunction (BEED) study, carried out in the Mirpur urban slum of Dhaka, provided a distinctive opportunity to explore the involvement of the duodenal microbiota in the onset of environmental enteric dysfunction (EED) in children and its link to stunted growth [3]. 110 children, aged 18 ± 2 months, who met the criteria for stunting or being at risk for stunting, failed to respond to nutritional intervention, and for whom consent was obtained, underwent esophagogastro-duodenoscopy (EGD). The BEED study also conducted EGD on thirty-eight malnourished women aged 18–45 years (BMI < 18.5 kg/m²) living in the resource-poor area of Mirpur, who did not respond to an egg, milk, and micronutrient-based nutritional intervention similar to that provided to children [3]. For this study, an operational classification of EED was established based on three histopathologic features observed in hematoxylin and eosin-stained tissue sections: inflammatory cell infiltration in the lamina propria, blunting or atrophy of the small intestinal villi, and crypt hyperplasia or elongation. The results, however, showed no statistically significant correlation between the length-for-age (LAZ) scores of the children.

Interestingly it was observed that 90% of the women had histopathologic evidence of enteropathy. The histopathologic features of their duodenal biopsies mimicked what was documented in the children with EED, including reduction in villus height and number, damage to the small intestinal epithelial barrier, and persistent inflammatory cell infiltration in the lamina propria [4–6]. The study done by *Hossain et al.* revealed that malnourished adults had a significantly higher frequency of subtotal villous atrophy, crypt hyperplasia, and marked cellular infiltration than the healthy controls [5]. Of the 38 women who underwent endoscopy, matched duodenal aspirates, fecal samples, and plasma samples from 22 [BMI 17.5 ± 0.9 kg/m^2^; 26.6 ± 8.2 years old] women were obtained. Matched plasma samples and duodenal biopsy specimens were obtained from 84 out of 110 children. A “core group” of 14 bacterial taxa was identified, each present in at least 80% of the EED-associated aspirate samples [4]. The absolute abundance of 14 shared bacterial strains isolated from children’s duodenal samples exhibiting histopathologic signs of EED and not commonly recognized as enteropathogens - was found to be inversely correlated with linear growth, and positively correlated with components of the expressed duodenal proteome involved in immuno-inflammatory responses.

Based on these findings, in this proposal, we will test the hypothesis that small intestinal microbiota contributes to small intestinal enteropathy and malnutrition in young Bangladeshi women of childbearing age. Based on the hypothesis that transmission of microbiota of mothers with EED to their children perpetuates intergenerational undernutrition, an interventional component will be included involving the administration of a specially designed nutritional supplement aimed at improving gut microbiota in pregnant and non-pregnant low BMI women, termed as the microbiota directed balanced energy protein (MD-BEP).

### Nutritional intervention

Conventional nutritional interventions or low-cost water, sanitation and hygiene (WASH) interventions were found ineffective in reversing EED-related malnutrition [7–9], warranting microbiome-targeted food and other interventions. Recently, nutritional intervention prototypes have been formulated using locally sourced, cost-effective, and culturally appropriate complementary foods in Bangladesh that are commonly consumed. Preclinical tests using gnotobiotic mice and piglets, which were colonized with gut microbiota from Bangladeshi children with acute malnutrition, revealed that these nutritional formulations include elements that increase the presence and positive functions of growth-supporting gut bacteria - bacteria that are usually reduced in these children. Subsequently, multiple microbiota-directed complementary food (MDCF) formulations were evaluated in a preliminary proof-of-concept study involving 12 to 18-month-old children with moderate acute malnutrition (MAM) residing in the Mirpur slum. This controlled, one-month, four-group feeding trial compared three different MDCFs to a standard rice-lentil-based ready-to-use supplementary food (RUSF), which was not designed to influence the gut microbial ecosystem. Among the tested MDCFs, MDCF-2 stood out for its enhanced ability to (i) restore the gut microbiota of MAM-affected children to a composition similar to that of healthy children in the community, and (ii) induce beneficial changes in plasma protein profiles related to metabolism, bone development, immune regulation, and neurodevelopment [10, 11]. These outcomes support the hypothesis that correcting disruptions in gut microbial community development may represent a novel strategy for promoting healthy growth. MDCF-2 is composed of chickpea flour, peanut flour, soy flour, green banana, sugar, soybean oil, and a vitamin-mineral premix. Building on these findings, and in partnership with a major food manufacturer in Bangladesh, a shelf-stable packaged version of MDCF, containing green banana powder, was developed and named the MDCF shelf-stable foil pouch formulation.

The latest World Health Organization (WHO) antenatal care guidelines recommend balanced energy-protein (BEP) supplementation for pregnant women in nutritionally vulnerable populations, aiming to lower the incidence of stillbirths and small-for-gestational-age (SGA) births. Recent meta-analyses further support this recommendation, demonstrating that BEP supplementation during pregnancy significantly improves infant birth weight in undernourished populations [12–14]. In September 2016, the Bill and Melinda Gates Foundation convened an expert consultation to establish nutrient composition guidelines for affordable nutritional supplements intended for pregnant and lactating women in undernourished settings. The consultation reviewed various formulations previously used in BEP supplementation trials and assessed macronutrient and micronutrient requirements based on Dietary Reference Intakes (DRIs) proposed by the U.S. Institute of Medicine (IOM) and FAO/WHO. The panel recommended that women in such contexts receive a daily BEP supplement delivering 250–500 kcal and 14–18 g of protein. For high-risk populations with significant nutritional deficits, the serving size could be increased accordingly. Conversely, in settings with lower nutritional risk, the supplement could provide energy at the lower end of the recommended range [15]. Based on the recommendations, in this study, we developed a modified BEP formulation with the ingredients used in MDCF-2, which is aimed to improve the gut microbiota and are calling it microbiota directed balanced energy protein (MD-BEP). The other arm will receive another modified BEP developed with the ingredients used in RUSF and are calling it ready-to-use supplementary food-balanced energy protein (RUSF-BEP).

